## **13.0 CRITERIA FOR OUTCOME ASSESSMENT AND ENDPOINT EVALUABILITY**

### **13.1 Criteria for Therapeutic Response/Outcome Assessment**

This study is not designed to assess a therapeutic response.

### **13.2 Criteria for Study Endpoint Evaluability**

Protocol participants will become evaluable for the safety analysis at the time of study drug administration. Patients who are removed within the DLT period due to reasons not associated with the trial primary endpoint will be replaced.

Five patients will be observed at each dose level. If  $> 20\%$  of patients within a cohort experience a grade 2 or higher adverse event that is considered attributable to the drug and clinically significant, dose escalation will be stopped at that level, and the prior dose level will be considered the MTD. If the desired response endpoint (sustained grade 4 fluorescence for 90 minutes or longer) is achieved in 3 patients at a single dose level, another 5 patients will be enrolled at this dose level. If sustained subjective grade 4 fluorescence is again observed in 3 of the next 5 patients, escalation to an incremental dose (not to exceed  $+0.5\text{mg/kg}$ ) may be assessed in 5 additional patients to measure any potential improvement over the prior dose. Improvement is defined as sustained visualization of the obturator at grade 5 observed in 3/5 patients at the incrementally higher dose. If no improvement is seen at the incremental dose, the previous dose would be considered an acceptable imaging dose. If improvement is observed, another 5 patients will be enrolled at this dose. If sustained subjective grade 4 fluorescence is not observed in 3 of this second group of 5 patients, this will not be a sufficient dose, and escalation to an incremental dose (not to exceed  $+0.5\text{mg/kg}$ ) will be tested. Once an acceptable imaging dose level has been selected, an expansion cohort will be undertaken, which will not exceed 20 patients. The expansion cohort may be stopped at any point prior to reaching the 20th subject if it is deemed that adequate safety and efficacy information has been collected.

#### Secondary Objectives:

Pharmacokinetic analysis will be conducted by MSK. Change from baseline for the Neuropathy Impairment Scale will be described at the three postoperative timepoints by giving the quartiles and top 10% highest scores. Surgeon subjective assessments of obturator nerve fluorescent intensity will be calculated using general estimating equations with time, dose and a time x dose interaction term using a binary endpoint of adequate fluorescence (score of 4 or 5). This analysis will be repeated for blue fluorescence vs. white-light by comparing the coefficient and standard error thereof for dose and time x dose interaction. No quantitative analyses are planned for *in vivo* and/or *ex vivo* fluorescent signal of presumed nerve tissue with corresponding histologic evaluation in patients undergoing a wider resection.

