### Secondary Objectives:

- To continue visual assessment of the obturator nerve using a subjective intensity scale assessed during the course of surgery.

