If sustained subjective grade 4 or higher fluorescence (acceptable fluorescence) is observed for 90 minutes or longer in 3 of 5 patients tested at that dose level, another 5 patients will be enrolled at this dose. If sustained subjective grade 4 fluorescence is not observed in 3 of this second group of 5 patients, this will not be a sufficient dose and escalation to the next highest level will be tested. However, if sustained subjective grade 4 fluorescence is again observed in 3 of the next 5 patients, escalation to an incremental dose (not to exceed +0.5mg/kg) may be assessed in 5 additional patients to measure any potential improvement over the prior dose.

If obturator nerve fluorescence is not sustained at a grade 4 level for at least 90 consecutive minutes in at least 3 of the 5 patients at a dose, the dose will be escalated to the next level, and 5 more patients will be enrolled. This will be repeated sequentially up to the maximum evaluable dose (2.25 mg/kg) if sustained fluorescence is not achieved at a lower dose.

If subjective sustained grade 4 fluorescence is not achieved at any of the dose levels and no DLTs are observed at any dose level, the maximal subjective sustained grade level of fluorescence will be calculated across all dose levels. The lowest dose associated with at least

a subjective sustained grade 3 level of fluorescence will be considered the safe and effective dose.

If sustained grade 3 fluorescence is not achieved in 3 of 5 patients at any dose level, the agent will not be considered to have reached a clinically useful endpoint, and the protocol will not expand directly to Part 2. We will evaluate the safety and clinical data and consider a protocol amendment to the IRB requesting to administer a higher dose than the current maximum in the protocol.

Once the imaging dose of Illuminare-1 is established at a no-DLT level, an expansion cohort of up to 20 patients will be evaluated at this dose. The safety and effectiveness of the agent will be assessed in the same manner as during the dose escalation phase of the study as described above. Briefly, adverse events through the first postoperative visit ( $10 \pm 5$  days) will be used to assess for toxicity and if the trial can continue accrual. If  $>20\%$  of patients experience a grade 2 or higher adverse event that is considered attributable to the drug and clinically significant, this will be considered unacceptable and the trial will be stopped..

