## **Part 1**

1. Surgery with patients under anesthesia is anticipated to have a duration of 4-6h and will be conducted per routine.
2. An arterial line will be placed to monitor vital signs and allow for sequential blood draws throughout the case. Arterial lines are placed in select patients undergoing prostatectomy, but this is not standard for all cases. Patients will be informed that this monitoring will be additional to the standard anesthesia anticipated for such cases and will be reviewed in the informed consent document.
3. Blood will be drawn at baseline and at 15, 30, 120, 240, 480 minutes ( $\pm$  10 min), 12 hours ( $\pm$  1h), 18 hours ( $\pm$  2h), and 24 hours ( $\pm$  2h) after administration for

pharmacokinetics analysis in all patients. In addition, a minimum of 3 patients in each dose cohort will also have blood drawn at 48 hours (+/- 24h) and 72 hours (+/- 24h) after administration for pharmacokinetics analysis.

4. The obturator nerve will be used as the reference nerve, and intensity of fluorescence will be recorded. The obturator was selected as the reference nerve for the following reasons: it is a nerve structure universally encountered during all pelvic lymph node dissections, owing to its anatomically consistent location; fat, vasculature, lymphatics, and muscle structures are adjacent and can serve as background tissues for fluorescent intensity comparisons; it is a myelinated structure that would be anticipated to fluoresce after administration of Illuminare-1 in humans; and it has fluoresced in all animal models used to date when assessed. Fluorescence will be graded on a 5-point scale.

Intensity of Fluorescence Subjective Scale:

1 = no fluorescence of obturator nerve

2 = no difference in contrast between background enhancement and reference nerve

3 = minimal contrast between obturator nerve fluorescence and background normal tissues

4 = moderate contrast between obturator nerve fluorescence and background normal tissues

5 = maximal contrast between obturator nerve fluorescence and background normal tissues

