5. Surgeon subjective assessments of obturator nerve fluorescent intensity will be measured at 30 minutes ( $\pm$  5 minutes) after intravenous administration of Illuminare-1 and every 20 minutes ( $\pm$  5 minutes) thereafter, as long as the measurement of fluorescent intensity will not negatively affect the ongoing portion of the surgical procedure. If the fluorescent intensity of the nerve cannot be assessed at a specific time point because it would disrupt the flow of the surgical case, this will be recorded, and the assessment will be made at the next scheduled time point. The anticipated time required to make a subjective assessment of the fluorescent intensity of the obturator nerve, on the basis of preclinical observations, is between 30 and 60 seconds per assessment. We anticipate this may add an additional 7-15 minutes to the procedure with the patient under anesthesia. One surgeon observer will record the obturator nerve to background fluorescent intensity at each time point.

6. Simultaneously, video recordings will be captured for *post hoc* analysis under white light and blue light for objective, quantitative assessment of NMR. These data will be used to inform future hardware and software optimization for later studies.
7. Simultaneously, 24 hour ECGs will be collected via Holter monitor for *post hoc* analysis.
8. Resection of the nerve bundles and histologic confirmation are not mandatory and are not expected as part of the protocol. They will be performed only on structures that would normally be removed as part of the standard of care surgery the patient will receive. Patients with high-risk disease features (high PSA, abnormal digital rectal exam, Gleason sum 8 or higher disease) or MRI features concerning for extracapsular extension of disease are more likely to have a wider resection of neurovascular tissues to achieve a negative surgical margin. We anticipate the wide resection of neurovascular bundles will be infrequently performed—in  $\leq 5$  patients total—during the dose-escalation part of the study; this number will depend on the cohort of patients enrolled and the clinical risk factors associated with the individual patients' prostate cancer. There may be a higher number of patients with these disease characteristics enrolled during the expansion phase of the protocol.

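### The only planned dose-time model of obturator fluorescence cuts the 1–5 score at 4; adding a model of the full score would recover collected information at almost no cost

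*Protocol*

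**What the plan says.** Section 4.2 (Part 1, items 4 and 5) sets the measurement: "Fluorescence will be graded on a 5-point scale". The first score is taken 30 minutes after injection, with further scores every 20 minutes where surgery allows: "One surgeon observer will record the obturator nerve to background fluorescent intensity at each time point". The Part 2 secondary objective in Section 2.0 is stated on the scale: "To continue visual assessment of the obturator nerve using a subjective intensity scale assessed during the course of surgery".

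Section 14.0, Secondary Objectives, specifies the analysis as "general estimating equations with time, dose and a time x dose interaction term", "using a binary endpoint of adequate fluorescence (score of 4 or 5". The protocol plans no other model of these scores.

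Elsewhere the protocol uses three different cuts of the same scale:

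- **Grade 4.** Section 4.2 adds patients at a dose if "sustained subjective grade 4 or higher fluorescence (acceptable fluorescence) is observed for 90 minutes or longer in 3 of 5 patients". The response definition in Section 14.0 also uses grade 4.
- **Grade 5.** Section 13.2, on the incremental dose: "Improvement is defined as sustained visualization of the obturator at grade 5 observed in 3/5 patients at the incrementally higher dose".
- **Grade 3.** Section 4.2, if sustained grade 4 is reached at no dose and there are no DLTs: the lowest dose with at least "a subjective sustained grade 3 level of fluorescence will be considered the safe and effective dose".

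**The concern.** The binary endpoint treats grades 4 and 5 as the same result, and likewise grades 1, 2 and 3. Information already collected is dropped in a trial that starts with 5 patients per dose level and enrols at most 50. The resulting dose and time-course estimates are meant to inform a phase II design, and they will be less precise than the data allow.

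The model also cannot show a dose effect that lies wholly within 4 to 5 or wholly within 1 to 3. The protocol itself treats both distinctions as meaningful when it defines improvement at grade 5 and a fallback at grade 3.

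**Working it through.** **1. The plan's own figure.** The only fluorescence probabilities stated are in Section 14.0: about 80%, 25% and about 10% for meeting the response criterion at true response rates of 75%, 50% and 40%. They reproduce as P(at least 3 of 5)²: 0.8965² = 0.804, 0.5² = 0.250 and 0.3174² = 0.101. They concern the counting rule. No power, error rate or effect size is stated for the GEE, so there is no figure to reproduce for the analysis at issue.

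**2. Information lost by the cut.** For independent scores under proportional odds, the efficiency of a binary cut relative to the five-category score is 3p(1 − p) / (1 − Σpᵢ³), where p is the probability of a score of 4 or 5 and pᵢ are the grade probabilities. The distributions are assumptions; the documents give none.

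| Assumed probabilities, grades 1 to 5 | p | Relative efficiency |
|---|---|---|
| .02 .03 .45 .45 .05 | 0.50 | 0.750 / 0.818 = 0.92 |
| .10 .15 .25 .30 .20 | 0.50 | 0.750 / 0.945 = 0.79 |
| .20 each | 0.40 | 0.720 / 0.960 = 0.75 |
| .35 .25 .20 .15 .05 | 0.20 | 0.480 / 0.930 = 0.52 |
| .02 .03 .10 .40 .45 | 0.85 | 0.383 / 0.844 = 0.45 |
| .45 .30 .15 .08 .02 | 0.10 | 0.270 / 0.878 = 0.31 |

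The cut costs little when scores split between 3 and 4, and a lot when most doses lie well below or well above the threshold.

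**3. Power for dose, patient-level permutation test (5% two-sided).** Scores come from a latent normal variable with cuts 1 SD apart, 6 looks from 30 to 130 minutes, and three splits of between- and within-patient variance. Means are set so that the probability of grade 4 or higher at all looks equals the stated response rate. The rates 40%, 50% and 75% come from Section 14.0; 20% and 60% are assumed. The test compares the patient's share of scores at 4 or 5 with the patient's mean score.

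| Response rates by dose | Patients | Cut at 4 | Full score | Gain (points) |
|---|---|---|---|---|
| 20/40/75% | 5/5/10 | 67–69% | 76–85% | 9 to 16 |
| 20/40/75% | 5/5/30 | 86–90% | 91–96% | 5 to 6 |
| 40/60/75% | 5/5/30 | 45–50% | 53–58% | 7 to 12 |
| 50/75% | 10/5 | 3–5% | 15–16% | both uninformative |

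**4. The planned model terms.** A second simulation fitted GEEs with time, dose and time x dose: logistic on score 4 or higher, and linear on the 1–5 score. It assumed 5 doses of 5 patients, 6 looks, latent within-patient correlation 0.5, bias-reduced standard errors and 400 runs. Power for the dose term, binary against full score, was 30% v 60%, 40% v 55% and 48% v 60% for a moderate slope, and 67% v 95%, 84% v 92% and 87% v 94% for a steeper one. With no dose effect, rejection rates were 3.5–7.8% (binary) and 5.8–7.5% (full score). Error control is therefore imperfect, and these wider gaps support the direction more than the size.

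**5. Shifts inside the merged grades.** In the same GEE set-up, if dose only moves patients from 4 to 5 (probability of 4 or higher fixed at 0.80), rejection is 6% for the cut and 59% for the full score. If dose only moves patients from 2 to 3 (probability of 4 or higher fixed at 0.05), it is 13% and 76%. The true binary effect is nil in both cases, so the 13% is sparse-data false positives.

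**6. Can the binary model be fitted?** At a 75% sustained response rate, the chance that all 15 patients of a 10-versus-5 comparison hold grade 4 or better throughout is 0.75¹⁵ = 0.013. When the first and third scenarios of step 3 were re-simulated with a linear dose term, some dose level was all 0 or all 1 in 5–11% of runs, but the logistic model with time, dose and their interaction was separated in under 1%.

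**The case against.** The strongest defence is that the cut is not arbitrary. Grade 4 or higher is what the protocol calls acceptable fluorescence. The primary objective, the response definition and the expansion-cohort re-evaluation all rest on it, and a model of its probability by dose and time estimates that quantity directly. This stands, and it is why the binary result should be kept.

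A reader might infer that the cut distorts the choice of dose, because the grade-5 and grade-3 rules cannot be seen in the model. The documents do not support this. Both rules are patient counts on the graded scale, and Section 4.2 also has the maximal sustained grade calculated across doses when grade 4 is not sustained at any of them. The GEE is secondary and drives no escalation or selection step.

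A reader might also infer that the dose coefficient does not exist when two doses both reach grade 4, or neither does. That is not a general result. The rule needs 3 of 5 patients, not all, and the planned model is not restricted to two dose levels. Only a near-constant outcome breaks the model, and step 6 shows that to be uncommon. The grade-3 fallback, with almost all zeros, is where it is most likely. A dose level that is all 0 or all 1 would matter more if dose were fitted as a category; Section 14.0 does not say how it is coded.

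Two further objections carry weight. The simulations use a latent-shift model, which favours the full score, and no cumulative-logit model was fitted. Proportional odds is also open to doubt at the bottom of the scale, where grades 1 and 2 both mean that the nerve is not distinguished. Both argue for adding a full-score model rather than deleting the binary one. Finally, a statistical analysis plan that is not shown may contain such a model; the point here is the method that the protocol states.

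**Conclusion.** The point holds as a cheap improvement, not as an error that threatens the trial. The only planned dose-time model discards information that the trial collects. Relative efficiency is about 0.3 to 0.9, and the loss of power is about 5 to 16 points in the permutation scenarios. These sizes rest on assumed grade distributions, correlations and effects. The direction is the same in every scenario run, and the blindness to 4-versus-5 and 3-versus-lower shifts follows from the definition of the endpoint. Dose decisions are unaffected, and the binary model would usually be estimable.

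**What to change.** In Section 14.0, Secondary Objectives:

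- Add, as the main dose-time analysis, a repeated-measures model of the full 1–5 score with time, dose and time x dose. Either a cumulative-logit or a mean-score model would do, fitted as a GEE or mixed model, with small-sample corrected or patient-permutation inference.
- Keep the probability of a score of 4 or 5 by dose and time as the acceptability summary, and also report the probability of grade 5.
- Say which model the blue-versus-white-light repeat uses.
- Leave every escalation and dose-selection rule unchanged.

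The cost is a sentence or two in the protocol and a little more analysis work, with no new patients, visits or measurements. The real downside is a proportional-odds or equal-spacing assumption that can be only weakly checked with 5 patients per dose. Comparing its fitted probability of a score of 4 or 5 with the retained binary result gives a partial check.

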## 1.0 PROTOCOL SUMMARY AND/OR SCHEMA

**Title:** Phase I Trial of Real-Time Intraoperative Fluorescent Imaging of Nerve Structures Using Illuminare-1, A Novel Myelin-Binding Fluorophore

This is a single-arm, open-label, phase I study of Illuminare-1, a novel myelin-binding fluorophore created with the goal of reducing inadvertent iatrogenic injury during surgery by allowing fluorescent identification of nerves. In Part 1, the dose-escalation phase, we will investigate the safety of Illuminare-1 at a minimum of 3 dose levels in patients undergoing minimally invasive radical prostatectomy and bilateral pelvic lymph node dissection. Additionally, the pharmacokinetics of a single injection of Illuminare-1 and the time to acceptable visualization of the obturator nerve, a universally encountered reference nerve, will be determined. Illuminare-1 will be evaluated at a minimum of 3 dose levels or until dose-limiting toxicities (DLTs) are experienced or sustained nerve visualization is observed. In Part 2, to provide additional safety data, collect data on the ability of the agent to visualize the obturator nerve and periprostatic nerves (to inform the design of a phase II study), and provide data for future hardware and software optimization, an expansion cohort of up to 20 patients will receive the dose identified in Part 1. Subjects will receive standard of care surgery, and Illuminare-1 will not be used to make surgical treatment decisions. Up to 50 patients will take part in the study; study enrollment is anticipated to take less than 18 months with roughly two months of follow up after the last patient receives the agent; total time for the protocol is estimated to be 20 months.

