### Exploratory Objectives:

- For patients in the expansion cohort once the safe and effective dose has been identified, to assess visualization of the neurovascular bundles under blue-light fluorescence, compared with white-light, at multiple time points during standard of care minimally invasive radical prostatectomy.
- To correlate the *in vivo* and/or *ex vivo* fluorescent signal of any presumed nerve tissue with corresponding histologic evaluation in select patients undergoing a wider surgical resection as part of routine surgery (i.e., patients with higher-stage disease for whom non-nerve-sparing approaches would normally be used). This would apply to all patients in the study where applicable.

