Although it is not anticipated to occur, if in the expansion cohort sustained grade 4 fluorescence fails to occur in  $>25\%$  of patients, this dose will be reevaluated to determine whether it is indeed an acceptable dose for visualization. We will assess the fluorescent response and safety of the next lower and higher doses tested to see whether these need to be explored for further investigation and will submit the appropriate amendment request to the IRB.

In the expansion cohort, observation of the periprostatic nerves in the neurovascular bundle will be included, in addition to assessment of obturator nerve fluorescence as performed in Part 1 of the protocol. One future aim for this agent will be to aid identification of the periprostatic neurovascular bundles, with the goal of improving nerve-sparing surgery. It is not known how well these small neurovascular bundles will fluoresce with this agent in humans and at what time points during surgery the nerves will be visualized. Additionally, with a heavily myelinated nerve such as the obturator, it is unknown whether an optimal signal will result in a similar fluorescent signal in the smaller and variably myelinated nerves in the periprostatic neurovascular bundles. In dog models (which closely resemble human anatomy in the prostatic region), we were able to accurately identify and dissect individual periprostatic nerves as small as 65 microns in diameter; therefore, we anticipate this agent will be able to enhance visualization of similar structures in humans. We will evaluate the neurovascular bundles before opening the endopelvic fascia, during the nerve-sparing portion of the prostatectomy (if performed as part of the standard of care surgery), and once the prostate has been removed.

One surgeon observer will assess whether structures corresponding to presumed nerve tissues within the periprostatic neurovascular bundles can be seen under blue-light conditions (binary result: Yes vs. No). If a positive response is recorded, the surgeon will rate their confidence on a 4-point scale regarding whether the fluorescence represents periprostatic nerves (1 = least confident to 4 = most confident). We will look *ex vivo* at the region of the prostate corresponding to neurovascular bundles after removal of the prostate to see whether

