9. Adverse events will be recorded and reported as necessary for the first 24 h after injection or until discharge and at the first postoperative visit ( $10 \pm 5$  days). Adverse events will also be collected by phone at  $30 (\pm 5)$  days, and in person at the follow-up visit corresponding to the first postoperative PSA lab assessment, which typically occurs approximately 7 weeks after surgery ( $45 \pm 10$  days). Blood will be drawn at each in person follow-up visit for potential future research purposes under MSK IRB#06-107 or MSK IRB #12-245.

## Part 2

1. In this dose-expansion part of the study, we will continue to assess the safety of Illuminare-1 at the dose selected following completion of Part 1.
2. In this part of the study, we will evaluate, in addition to the obturator nerve, the neurovascular bundles before opening the endopelvic fascia and during the nerve-sparing portion of the prostatectomy (if performed as part of the standard of care surgery). We will look at the neurovascular bundles after removal of the prostate to see whether a fluorescent signal consistent with nerve structures within the neurovascular bundle can be identified. One surgeon observer will record whether presumed nerve structures are visualized under blue-light conditions (Yes vs. No); if nerve structures are seen, the confidence level of this assessment will be recorded (graded scale of 1-4, as described previously). The extent of surgery performed and the degree of nerve sparing that was undertaken will not be altered on the basis of the fluorescence of the

presumed location of the neurovascular bundles. This will be optionally performed during Part 1 if possible. The sensitivity and specificity of this agent's ability to accurately localize the small nerves within the neurovascular bundles have not been established, and no surgical decisions will be made on the basis of the fluorescence of structures in the periprostatic regions.

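### The planned blue-versus-white-light comparison does not estimate the contrast that its exploratory objective asks for, and no white-light rating is defined or scheduled.

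*Protocol*

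**What the plan says.** Protocol Section 14.0 (Secondary Objectives) first describes a GEE for the surgeon's obturator nerve scores with time, dose and time x dose, "using a binary endpoint of adequate fluorescence (score of 4 or 5"). It then says this analysis will be "repeated for blue fluorescence vs. white-light by comparing the coefficient and standard error thereof for dose and time x dose interaction".

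The only objective that compares the two light modes is the first exploratory objective in Section 2.0. Its population is given as "For patients in the expansion cohort once the safe and effective dose has been identified", and its aim is "to assess visualization of the neurovascular bundles under blue-light fluorescence, compared with white-light, at multiple time points". Section 1.0 says of that cohort that "an expansion cohort of up to 20 patients will receive the dose identified in Part 1".

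For the bundles, Section 4.2 has one surgeon judge whether presumed nerve tissue "can be seen under blue-light conditions (binary result: Yes vs. No"), with a 1 to 4 confidence grade if the answer is Yes. The Part 2 list in the same section repeats this: "One surgeon observer will record whether presumed nerve structures are visualized under blue-light conditions (Yes vs. No"). Three looks are named: before the endopelvic fascia is opened, during nerve sparing if that is performed, and after the prostate is removed.

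**The concern.** The sentence in Section 14.0 and the objective in Section 2.0 differ in the nerve examined, the rating used and the quantity estimated. The objective asks whether the bundles are seen better under blue light than under white light. The analysis carries over an obturator fluorescence endpoint and compares how that endpoint changes with dose. It also needs a white-light outcome, and the protocol defines none.

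At stake is whether the trial can answer one of its own exploratory questions. The analysis model can be reworded later. A rating made by the surgeon during the operation cannot be added once the operation is over.

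**Working it through.** The protocol gives no figure for this analysis, so there is none to reproduce. The check has four steps.

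**1. Objective, data and model side by side**

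| | Objective (Section 2.0) | Data collected | Model (Section 14.0) |
|---|---|---|---|
| Nerve | Neurovascular bundles | Bundles and obturator | Obturator |
| Patients | Expansion cohort | Bundles: Part 2, optional in Part 1 | Not stated |
| Outcome | Visualization, blue against white | Bundles: Yes/No under blue. Obturator: 5-point fluorescence contrast | Score of 4 or 5 |
| Quantity | Blue against white | – | Dose and time x dose coefficients |

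The Section 11.0 schedule lists subjective fluorescence assessments of the obturator nerve and of the bundles. It has no row for a white-light rating. Section 4.2 (Part 1, item 6) captures white light on video for post hoc quantitative nerve-to-muscle ratio, which is neither a 4/5 score nor a Yes/No.

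**2. What the compared coefficients measure**

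For light mode m, time t and dose d, the model is

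logit P(m) = a(m) + b(m)·t + c(m)·d + e(m)·t·d.

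The blue-minus-white difference on this scale, with Δ meaning blue minus white, is

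Δa + Δb·t + Δc·d + Δe·t·d.

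The plan compares only c and e. If c and e were the same in both modes, the comparison would show nothing, however large Δa was. Both modes are also viewed in the same patient, so

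Var(Δc) = Var(c blue) + Var(c white) − 2·Cov(c blue, c white).

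The coefficients and standard errors of two separate fits do not supply the covariance.

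**3. Estimability**

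In the expansion cohort d is constant. The dose column is then d times the intercept, and the time x dose column is d times the time column. Numerical rank of the four-column design matrix:

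| Patients (doses in mg/kg; mixes assumed) | Time points | Columns | Rank |
|---|---|---|---|
| Expansion cohort, 20 patients, one dose | 3 or 6 | 4 | 2 |
| Part 1 (5 at 0.25, 10 at 0.75, 5 at 1.25) plus 20 at 0.75 | 3 or 6 | 4 | 4 |
| Three optional Part 1 bundle patients at other doses, plus 20 | 3 or 6 | 4 | 4 |

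Dose and time x dose are therefore not estimable within the expansion cohort alone. They are estimable once Part 1 doses are pooled in. Pooling does not supply a white-light outcome, and it does not change what c and e measure.

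**4. Precision of a paired comparison**

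The inputs are 20 patients (the cohort maximum), an assumed difference D = 0.30 and an assumed discordant proportion q. Neither D nor q is in the protocol. At one time point

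SE = √[(q − D²)/20].

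- q = 0.30 (the smallest possible with D = 0.30): √(0.21/20) = 0.102; 1.96 × 0.102 = 0.20
- q = 0.40: √(0.31/20) = 0.124; 1.96 × 0.124 = 0.24
- q = 0.60: √(0.51/20) = 0.160; 1.96 × 0.160 = 0.31

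The half-width is about 20 to 31 points. This is a large-sample approximation used at n = 20.

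**The case against.** Section 14.0 does not confine the comparison to Part 2. It says the preceding analysis is repeated, and that analysis makes sense only across dose levels. Section 4.2 allows the bundle assessment optionally in Part 1. A reader might infer that the analysis cannot be run because the cohort has one dose. The documents do not support that as a flat statement: non-estimability follows only if the sentence is tied to the Section 2.0 objective. That link is natural, since there is no other blue/white objective, but it is not written down.

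A reader might also infer that no white-light data exist. That is wrong. Sections 4.1, 4.2 and 10.0 provide for video under both lights, and a later reading of that video could in principle yield a rating. The protocol defines no such reading and gives the video other uses: nerve-to-muscle ratio and hardware and software development.

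A third inference is that a white-light model would have no finite coefficients. An illustrative logistic GEE with every white-light outcome set to zero did show perfect separation (intercept about −27.6, slopes zero). But the protocol does not say how the nerve would score under white light, so this rests on an assumption.

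Finally, the objective is exploratory. Section 1.0 wants visualization data to inform phase II without naming a blue/white contrast, and Section 3.0 leaves the comparison with white light to later studies. It would go too far to say that the phase II design loses its basis, because the blue-light Yes/No and confidence data remain. The choice of paired model could also be left to a statistical analysis plan.

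What stands after all this is the mismatch of nerve, rating and quantity, and the absence of a defined white-light rating.

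**Conclusion.** The point holds in a limited form. As written, the blue/white sentence does not estimate the contrast in the only blue/white objective. It uses a different nerve and rating, and it compares dose slopes instead of light modes. Its two terms are not estimable within the expansion cohort alone (rank 2 of 4) and are estimable only with Part 1 doses pooled in. On either reading, no white-light rating is defined or scheduled.

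The consequence is modest. One exploratory objective goes unanswered, and no escalation, safety or expansion rule uses it. The conclusion about estimability rests on linking Section 14.0 to the Section 2.0 objective. The conclusions about the estimated quantity and the missing rating do not. The ±24-point figure (20 to 31 over the assumed discordance) illustrates what a paired comparison could deliver and does not measure the size of the error. The change should be made, because it is cheap and a prospective rating can only be collected during surgery.

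**What to change.** 1. **Data.** At each bundle look named in Section 4.2, have the same surgeon record Yes/No under white light just before switching to blue, with the 1 to 4 confidence grade if Yes. The grade is now worded in terms of fluorescence, so the white-light item should ask for confidence that the structure is nerve. Add the item to the Section 11.0 schedule.
2. **Analysis.** Replace the blue/white sentence in Section 14.0 with a within-patient paired comparison of bundle visualization by light mode. Examples are a GEE with light mode, time and their interaction clustered by patient, or an exact McNemar test at each time point. Omit dose terms for the expansion cohort, and state whether optional Part 1 bundle looks are included.

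**Cost.** One extra form item and a few seconds per look. Section 5.2 describes white-light modes on the same system, and Section 10.0 already places the camera for viewing under both lights. Surgical decisions are unaffected. The main limitation is that the surgeon is unblinded and the order is always white then blue, so the white-light answer may colour the blue-light one. The report should say so.
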